### Setting and participants

We will randomly select two BGC sites in Imperial County, California to receive the final Girls PLAY program prototype, with the goal of enrolling 30 youth participants across both sites. To be eligible, the BGC site must be (1) located within Imperial Valley and (2) provide programming to girls ages 8–10. To be eligible to participate in the feasibility study, youth participants must (1) live in Imperial County, California; (2) identify as female; (3) be aged 8–10 years old at time of enrollment; and (4) enrolled at a BGC site participating in the feasibility study.

Data collection will occur at baseline (0 weeks) and post-intervention (week 10–12). All measures will be available in English and Spanish. Recruitment strategies will include BGC’s established outreach methods for recruiting potential parent and youth participants, including sharing study flyers via BGC listservs and within the BGC sites. The research team will also present during BGC staff-parent meetings to share more information about the study.

### Data collection

Data collection will include electronic or in-person surveys for youth, parents, and staff (pending preferences elicited in formative work); direct observation; device-based PA assessment; and use of administrative data. Table 2 provides an overview of study variables, assessment methods, and collection time point. We will use REDCap to distribute the survey links to participants. Surveys will be available in English and Spanish.

**Table 2 Tab2:** Single-arm feasibility study data collection

Variables	Assessment method	Time
**Primary outcomes**		
Recruitment capability	Administrative data	F/U
Data collection procedures	Administrative data	F/U
Intervention acceptability	Parent and Staff Surveys	F/U
Intervention appropriateness	Parent and Staff Surveys	F/U
Intervention feasibility	Parent and Staff Surveys	F/U
Participant attendance	Administrative data	F/U

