**Fig. 1 Fig1:**
[figure not shown]
United States Department of Health and Human Services’ Framework for Understanding Youth Sports Participation

Physical literacy is one of the most important elements in healthy, developmentally appropriate youth sport participation and PA [20]. Physical literacy is defined as when an individual has the physical competence (basic movement skills), knowledge, confidence, and motivation to be physically active throughout the life course [23]. Physical literacy and sport skill development can be improved when youth participate in a variety of sports (i.e., sport sampling) [20, 24]. Sport sampling (i.e., engaging in a variety of sports) is strongly recommended for youth under age 12 [25], reduces injury and burnout [26, 27], and provides opportunity to explore different movement types and develop a range of physical skills [20]. Further, physical literacy and sport sampling are guiding principles of the American Development Model, which is used to promote appropriate athlete development and sustained PA throughout the life course [28].

Rural areas face barriers around available sport options, qualified coaches, facilities, and school sport programs [29–33], and thus may experience fewer opportunities for sport sampling. Hispanic girls also report lack of social support for activity and a lack of confidence in their ability [34, 35]. Many individual-level determinants of sport participation align with self-determination theory (SDT), which posits that three fundamental needs (autonomy, competence, and relatedness) are the source of intrinsic motivation [36]. Higher levels of relatedness, autonomy, and perceived competence have been associated with sustained sport participation [37–39]. Further, SDT-centered instruction is associated with higher levels of motivation, self-esteem, and satisfaction of basic needs in a variety of sport settings [40–42].

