**Additional variables**		
Demographics	Staff, parent, and youth surveys	B

*F/U* follow-up, *B* baseline, *SDT* self-determination theory

BGC staff will receive $50 for completing post-intervention surveys and collecting administrative data throughout the intervention. Parents will receive $15 for completing pre- and post-intervention surveys. Youth will receive $50 for completing surveys pre- and post-intervention and an additional $50 for wearing the accelerometers for 1 week.

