### Study outcomes

#### Primary outcomes

The primary outcomes, based on the essential components of a feasibility study [81], will be (1) recruitment capability, (2) data collection procedures and outcome measures, (3) acceptability and suitability of the intervention and study procedures, and (4) preliminary participant response to Girls PLAY, including changes in key outcomes.

*Recruitment capability* will be measured via administrative data, with a feasibility metric of successfully enrolling 30 participants in the Girls PLAY program. *Data collection procedures* will be assessed, in part, by the number of study assessments completed, with a feasibility metric of at least 75% of participants completing assessments at both baseline and follow-up [82, 83]. *Acceptability* of the intervention will be measured via the Acceptability of Implementation Measure (AIM) [84]. *Appropriateness* of the intervention will be measured via the Intervention Appropriateness Measure (IAM) [84]. *Feasibility* of the intervention will be measured via Feasibility of Intervention Measure (FIM) [84]. The AIM, IAM, and FIM are written at a 5th grade level and have demonstrated strong psychometric properties [84]. The feasibility metric for the AIM, IAM, and FIM will be a mean score of ≥ 3. *Participant attendance*, a measure of preliminary evaluation of participant response, will be measured using administrative data, with a goal of participants attending, on average, ≥ 75% of in-person sessions [82, 83].

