Additionally, our partnership with BGC supports sustainability and scalability of the Girls PLAY program and removes barriers around developing new systems and infrastructure. Building new infrastructure around youth sport is costly and time-consuming [112], particularly in rural settings where there are typically fewer available resources [112, 113]. Our partnership with BGC and the proposed program to be developed (Girls PLAY) can easily be expanded and implemented in BGC clubs nationally, and training existing BGC leaders within the community increases sustainability. Beyond the immediate evaluation of the Girls PLAY program feasibility, there is significant potential for this approach to be adapted and scaled across diverse contexts. While this study focuses on rural Hispanic girls, the underlying HCD framework provides a replicable process for tailoring interventions to other populations. Future research can explore the adaptation of the Girls PLAY program for other environments (e.g., urban) and populations (e.g., older age groups, cultural contexts). We plan to present the results of the feasibility study once the program is implemented so we can provide a foundation for future cross-cultural and cross-geographic applications and utilize the established infrastructure of the Boys and Girls Clubs of America to facilitate national dissemination.

There are several potential challenges with this work. To address recruitment and retention issues, we will work with BGC leaders to develop outreach strategies for youth, parents, and BGC staff. This will be impacted by potential staff turnover and staff investment in the program. Another potential challenge is that it may not be feasible to address all barriers identified in the Aim 1 community member interviews. However, findings from these interviews will be disseminated with the research community, which will be an important step in addressing barriers to rural girls’ sports participation and PA. Although interview results may not be generalizable to all rural populations, we will strive to include participants from a variety of rural areas. Further, given the qualitative nature of such work, the goal is not generalizability but achieving a depth of knowledge not easily obtained through quantitative methods.

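### Acceptability, appropriateness and feasibility are rated only at week 10–12, so families who stop and staff who leave are likely to be under-represented in three primary benchmark means

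*Protocol article*

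**What the plan says.** The Aim 3 feasibility study is single-arm, "with the goal of enrolling 30 youth participants across both sites". The Setting and participants section gives two time points: "Data collection will occur at baseline (0 weeks) and post-intervention (week 10–12").

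In Table 2, under primary outcomes, acceptability reads "Intervention acceptability Parent and Staff Surveys F/U" and appropriateness reads "Intervention appropriateness Parent and Staff Surveys F/U". Feasibility of the intervention has the same source and timing. The Primary outcomes section names the scales (AIM, IAM and FIM) and sets one benchmark for all three, a mean score of at least 3. It does not say whose scores enter that mean.

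The other primary benchmarks are enrolment of 30, "at least 75% of participants completing assessments at both baseline and follow-up", and average attendance of at least 75% of in-person sessions.

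The payment paragraph after Table 2 states: "BGC staff will receive $50 for completing post-intervention surveys and collecting administrative data throughout the intervention". The Data analysis section says that the amount of missing data will be reported for each variable without inferential missing-data analysis, and that analyses follow intention-to-treat. On recruitment and retention, the Discussion adds: "This will be impacted by potential staff turnover and staff investment in the program".

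**The concern.** The three scales are meant to show whether families and staff find the program acceptable, appropriate and workable. Those who find it least so are the most likely to have gone by week 10–12 and the least likely to answer a survey then. The plan expects some of this loss but has no planned contact at the time of leaving and no adjustment for missing ratings. A mean taken over those who respond is therefore likely to err upward, and each scale could meet its benchmark on responders alone.

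The gap is wider for staff than for families. Enrolment, completion and attendance are all counted on girls, so a staff member who leaves because delivery is too burdensome affects no primary benchmark and may give no rating. The article's limitations paragraph states that there are no pre-specified progression criteria, so these benchmark results will be a main basis for deciding on a larger trial.

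**Working it through.** The plan states no figure that this point disputes. The check asks how far non-response by leavers could move the benchmark mean.

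**Inputs from the article:** 30 girls; completion benchmark 75%; attendance benchmark 75%; scale benchmark mean ≥ 3.

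**Assumptions:** one parent rating per girl; the parents of lost girls give no rating; they would have averaged 1, 2 or 2.5; the observed mean among responders is 3.2. The article gives neither the scoring range nor expected scores.

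**1. Losses that the completion benchmark allows.** 0.75 × 30 = 22.5, so 23 girls are needed: 23/30 = 76.7% passes and 22/30 = 73.3% fails. Up to 7 can be lost.

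**2. Mean over all 30 parents,** (23 × 3.2 + 7 × s)/30, where s is the leavers' mean:

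| s | Calculation | All-30 mean | Against 3 |
|---|---|---|---|
| 1 | (73.6 + 7)/30 | 2.69 | below |
| 2 | (73.6 + 14)/30 | 2.92 | below |
| 2.5 | (73.6 + 17.5)/30 | 3.04 | above |

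The result changes sides at s = (90 − 73.6)/7 = 2.34.

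**3. Responder mean needed for the all-30 mean to reach 3,** (90 − 7 × s)/23:
- s = 1: 83/23 = 3.61
- s = 2: 76/23 = 3.30
- s = 2.5: 72.5/23 = 3.15

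An observed mean of 4.0 would stay above 3 even at s = 1: (92 + 7)/30 = 3.30. The problem is confined to observed means fairly near the threshold.

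**4. Staff.** The article gives no number of staff. Assume four, with three responders at 3.3 and one leaver. The observed mean is 3.3. The mean over all four is (9.9 + s)/4, which is 2.73, 2.98 or 3.10 for s = 1, 2 or 2.5. With so few raters, one missing score can decide the result.

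**5. Do the other benchmarks pick up the loss?** For girls, yes. If attendance is averaged over all 30 and the 7 leavers attend 0%, 25% or 50% of sessions, the other 23 must average (22.5 − 7a)/23, where a is the leavers' attendance: 97.8%, 90.2% or 82.6%. For staff, no benchmark responds.

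**The case against.** The strongest reply is that departures are not hidden. Completion and attendance are both primary, and step 5 shows that attendance becomes hard to meet when several girls stop early. This stands for girls, but it has limits: those benchmarks show that a girl left, not how her family rated the program, and they say nothing about staff.

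Second, follow-up timing is not an error in itself. A delivered program cannot be rated at baseline, and nothing in the article restricts the week 10–12 survey to families who completed. Survey links can go through REDCap, so the parent of a girl who stopped could still receive one. This also stands. The point is therefore that leavers are likely to be under-represented, not that the plan excludes them.

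Third, there are partial safeguards: missing data will be reported for each variable, explanatory interviews will be considered, and Aim 2 interviews staff, parents and youth during prototyping. Non-response would thus be visible. The interviews are not a commitment, however, and Aim 2 precedes the study whose benchmarks are at issue.

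A reader might also infer that nothing records why girls or staff leave, or that injuries would go unreported, the more so because the Background says that sport sampling "reduces injury and burnout". The document does not support that inference. Table 2 is an overview, the administrative data are not itemised, and an article commonly leaves withdrawal reasons and adverse-event recording to the full protocol. The injury remark is background rationale, not a study outcome.

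**Conclusion.** The point holds in a limited form. Three primary benchmark means rest on one survey at week 10–12, in a study that expects retention problems and staff turnover and will only count missing ratings. The likely direction of any error is upward. Its size depends on values that the article does not give: in the parent example an observed 3.2 becomes 2.69, 2.92 or 3.04, so the conclusion changes in two of the three assumed cases and not in the third. The example uses the largest loss that the completion benchmark allows, and it assumes that every lost girl means a silent parent and that these parents are less satisfied than the responders.

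It would go too far to say that the scores are biased, or that dropout disappears from the primary results. The staff part is the firmer one, because no primary benchmark registers a staff departure. This is an inexpensive improvement to the timing of three outcomes, not a flaw that invalidates the design.

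**What to change.** In Table 2 and the Primary outcomes section, schedule the same AIM, IAM and FIM survey at exit for parents of girls who stop and for staff who leave. Keep the week 10–12 survey for all other parents and staff. State that exit scores enter the benchmark mean, show each mean with and without them, and report the number of parent and staff non-responders. Showing both versions also lets the reader allow for the shorter exposure behind an exit rating.

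The cost is a few extra sends of an existing short survey. Some leavers will not reply, so the selection is reduced rather than removed, and the benchmark mean may become less favourable. The intervention, eligibility and sample size do not change.

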**Secondary outcomes**		
Physical activity	Youth-worn Accelerometer	B, F/U
Physical literacy	Youth survey, Direct observation	B, F/U
SDT constructs	Youth survey	B, F/U
Sport participation	Youth survey	B, F/U
**Additional variables**		
Demographics	Staff, parent, and youth surveys	B

*F/U* follow-up, *B* baseline, *SDT* self-determination theory

BGC staff will receive $50 for completing post-intervention surveys and collecting administrative data throughout the intervention. Parents will receive $15 for completing pre- and post-intervention surveys. Youth will receive $50 for completing surveys pre- and post-intervention and an additional $50 for wearing the accelerometers for 1 week.

### Study outcomes

#### Primary outcomes

The primary outcomes, based on the essential components of a feasibility study [81], will be (1) recruitment capability, (2) data collection procedures and outcome measures, (3) acceptability and suitability of the intervention and study procedures, and (4) preliminary participant response to Girls PLAY, including changes in key outcomes.

*Recruitment capability* will be measured via administrative data, with a feasibility metric of successfully enrolling 30 participants in the Girls PLAY program. *Data collection procedures* will be assessed, in part, by the number of study assessments completed, with a feasibility metric of at least 75% of participants completing assessments at both baseline and follow-up [82, 83]. *Acceptability* of the intervention will be measured via the Acceptability of Implementation Measure (AIM) [84]. *Appropriateness* of the intervention will be measured via the Intervention Appropriateness Measure (IAM) [84]. *Feasibility* of the intervention will be measured via Feasibility of Intervention Measure (FIM) [84]. The AIM, IAM, and FIM are written at a 5th grade level and have demonstrated strong psychometric properties [84]. The feasibility metric for the AIM, IAM, and FIM will be a mean score of ≥ 3. *Participant attendance*, a measure of preliminary evaluation of participant response, will be measured using administrative data, with a goal of participants attending, on average, ≥ 75% of in-person sessions [82, 83].

#### Secondary outcomes

To assess feasibility of collecting outcome data and preliminary changes in outcome measures (outcome 4), we will collect data on (1) PA levels, (2) physical literacy, (3) SDT constructs, and (4) sport participation at baseline (week 0) and post-intervention (week 10–12).

#### Physical activity

We will use Actigraph GT9X-BT (ActiGraph LLC, Pensacola, FL) to obtain a valid, objective measure of youth PA. We will examine minutes spent in moderate- to vigorous-intensity PA (MVPA). Accelerometers will be on an elastic belt and placed above the iliac crest of the hip. Data will be collected over 7 days (sample frequency of 30 Hz; 15-s epochs) during waking hours. We will use appropriate cut points to classify the time youth spent in respective activity intensities [85]. A research staff member will be onsite at the BGC to assist with placing the device on youth on day one and collecting the device on day seven.

*Physical literacy* changes among youth will be assessed using accelerometers and the Canadian Assessment for Physical Literacy, Second Edition (CAPL-2) [86, 87]. CAPL-2 measures physical, affective, and cognitive domains of physical literacy among ages 8–12 via three Physical Competence protocols (plank, Progressive Aerobic Cardiovascular Endurance Run [88], Canadian Agility & Movement Skill Assessment [89]), two Daily Behavior protocols (pedometer, self-reported PA), and a 22-item questionnaire assessing knowledge, motivation, and confidence (validated among ages 8–12) [86]. CAPL-2 allows for delivery of select individual protocols [86], and we will use accelerometers in place of pedometers and self-reported PA.

### SDT constructs

To measure changes in SDT constructs, we will conduct youth surveys. We will use the 9-item Autonomy-Supportive Coaching Questionnaire (ASCQ) to measure autonomy [90]. The ASCQ has been validated in ages 7–18, with α = 0.88 and α = 0.84 for internal consistency of interest in athlete’s input and for praising autonomous behavior, respectively [91]. Although the Spanish version of the ASCQ has not been validated among the age group of interest, it has been validated among Spanish athletes ages 12–17 and was found to have adequate temporal stability and internal consistency [92]. We will use an adapted version of the Perceived Competence Scale (4-item, PCS) to measure competence [36]. The PCS has a high face validity among children in a sport and PA context [93, 94]. Reliability of the perceived competence items was α = 0.90 [95]. We will use the 5-item acceptance subscale of the Need for Relatedness Scale (NRS) to measure relatedness [96]. The NRS has demonstrated adequate construct validity and internal reliability in research among young athletes [97, 98].

### Sport participation

Sport engagement will be assessed via youth survey examining current sport involvement (i.e., length of involvement, primary and secondary sport) and behavioral intention (e.g., “I intend to play sports this year”) adapted from items used in studies among similar age groups [99, 100]. Sport enjoyment will be measured using the adapted 5-item Enjoyment subscale of the Sport Commitment Questionnaire-2 [101–103]. Internal consistency and confirmatory factor analyses support reliability and validity among youth [103–105].

### Additional variables

In addition to the primary and secondary variables, we will also collect youth, parent, and staff demographic information via survey. We will collect youth demographic information such as age, race/ethnicity, and prior sports participation. We will also collect parent (e.g., sex, age, race/ethnicity, highest level of education, and household income) and staff (e.g., sex, age, race/ethnicity, number of years as a BGC staff member, role) demographic information.

### Sample size justification

Feasibility studies are not designed or powered to detect statistically significant effects on outcomes, but rather to assess whether key study processes are feasible. The target sample size of 30 participants for the feasibility study (Aim 3) was determined based on sample size recommendations for feasibility studies that typically range from 20 to 50 participants [106]. This sample size will allow us to assess recruitment capability and determine if our target of enrolling 30 participants is achievable; evaluate data collection procedures; examine acceptability, appropriateness, and feasibility measures; estimate variability in outcome measures; and assess participant attendance.

### Data analysis

Given the feasibility nature and sample size of the study, we will report the amount of missing data for each variable, rather than conducting any inferential missing data analysis. For the primary aim of feasibility, descriptive statistics will be used to examine and compare feasibility outcomes with pre-determined benchmarks. For the secondary aim of changes in key outcomes, we will report descriptive statistics (means, standard deviations, medians, interquartile ranges) and 95% confidence intervals for in mean daily minutes of MVPA, physical literacy, SDT constructs, sport enjoyment, and number of sports played at baseline and follow-up. We will also report the proportion of participants engaging in sport at each timepoint with 95% confidence intervals. Accelerometer data will be adjusted for wear time. These estimates of variability and precision will inform the design and sample size calculations for a future RCT. All analyses will be conducted using Stata 17.0 (StataCorp LP, College Station, TX). Analyses will follow intention-to-treat. Based on the quantitative findings, we will consider a sequential explanatory design in which qualitative interviews with a subset of participants are used to help interpret the quantitative results [107].

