A limitation of this study is the absence of pre-specified progression criteria to systematically determine whether to proceed to a full-scale randomized controlled trial. While we have established feasibility benchmarks for our primary outcomes (e.g., recruitment, data collection completion, acceptability, appropriateness, feasibility, and attendance), we have not specified a priori thresholds using a traffic light system as recommended by Avery et al. [116] and Mellor et al. [115]. The absence of such criteria limits our ability to make transparent, systematic decisions about progression to a definitive trial and may introduce subjectivity into the decision-making process. Future feasibility studies should incorporate clear progression criteria during the design phase to enhance methodological rigor and transparent reporting of progression decisions.

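### The primary feasibility benchmarks are to be judged on point estimates alone, while the secondary outcomes get 95% CIs, and the recruitment benchmark is a count with no denominator or period in the article

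*Protocol article*

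**What the plan says.** The protocol article's Data analysis section treats the two tiers of outcome differently. For the primary feasibility aim, "descriptive statistics will be used to examine and compare feasibility outcomes with pre-determined benchmarks". For the secondary outcomes, "we will report descriptive statistics (means, standard deviations, medians, interquartile ranges) and 95% confidence intervals", and the proportion of girls playing sport also gets an interval. The section then says that the resulting variability and precision estimates will feed the design of a later randomised trial. In context these are the secondary-outcome estimates.

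The benchmarks are in Primary outcomes:

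- Recruitment: "with a feasibility metric of successfully enrolling 30 participants in the Girls PLAY program".
- Data collection: "at least 75% of participants completing assessments at both baseline and follow-up".
- Acceptability, appropriateness and feasibility of the intervention: "The feasibility metric for the AIM, IAM, and FIM will be a mean score of ≥ 3". Table 2 assigns these three to parent and staff surveys.
- Attendance: an average of at least 75% of in-person sessions.

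Under Sample size justification, the figure of 30 "was determined based on sample size recommendations for feasibility studies that typically range from 20 to 50 participants"; no precision target is given. The Aim 3 Setting and participants section makes 30 the enrolment goal across two sites. The Discussion names the lack of progression criteria as a limitation: "we have not specified a priori thresholds using a traffic light system".

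**The concern.** The study exists to assess feasibility, yet the outcomes that answer that question are the ones without a planned interval. A future trial needs retention, attendance and uptake for its planning as much as it needs the standard deviation of activity minutes. With about 30 girls, a percentage set against a 75% line can look conclusive when the data fit a wide range of true rates.

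The recruitment benchmark has a related weakness. As worded in the article, a study that reaches 30 meets it equally whether few or many families were approached and whether enrolment was quick or slow. Taken alone, it gives neither an uptake proportion nor a recruitment rate to carry forward.

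**Working it through.** **The plan's own figure.** The sample size of 30 has no formula inputs (no precision target, alpha, power or effect size), so there is nothing to reproduce. It lies within the 20 to 50 range that the article cites.

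**Completion benchmark.** Inputs from the article: n = 30 and a threshold of 75%. 0.75 × 30 = 22.5, so a pass needs at least 23 girls, and 23/30 = 76.7%. This assumes that exactly 30 enrol.

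Wilson 95% interval with p = 0.7667, z = 1.96, z² = 3.8416:

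- Centre = (p + z²/2n) / (1 + z²/n) = (0.7667 + 0.0640) / 1.1281 = 0.736.
- Half-width = z × √[p(1 − p)/n + z²/4n²] / (1 + z²/n) = 1.96 × √(0.00596 + 0.00107) / 1.1281 = 0.146.
- Interval: 59.1% to 88.2%. The exact (Clopper-Pearson) interval is 57.7% to 90.1%.

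Probability of passing, P(X ≥ 23) with X ~ Binomial(30, p):

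| True completion | P(pass) |
|---|---|
| 55% | 0.012 |
| 60% | 0.044 |
| 65% | 0.124 |
| 70% | 0.281 |
| 75% | 0.514 |
| 80% | 0.761 |
| 85% | 0.930 |
| 90% | 0.992 |

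A pass is 0.7608/0.0435 = 17.5 times as likely at a true 80% as at a true 60%, but only 0.7608/0.2814 = 2.7 times as likely at 80% as at 70%. So it is good evidence against poor completion and weak evidence between 70% and 80%. By either interval method, a lower 95% limit of at least 60% needs 24 of 30, at least 65% needs 25, and at least 75% needs 28.

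**Attendance.** The article gives no SD. Assuming an SD of 15 to 30 percentage points and n = 30, the half-width is t × SD/√n with t = 2.045 on 29 df: 2.045 × 15/5.477 = 5.6 points, up to 2.045 × 30/5.477 = 11.2 points.

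**AIM, IAM and FIM.** The article gives neither an SD nor the number of respondents. Assuming an SD of 0.5 to 1.0, the half-width is 0.19 to 0.37 with 30 respondents. With an assumed 6 respondents (staff numbers are not stated) it is 0.52 to 1.05. Parents and staff could therefore differ greatly in precision, and a pooled mean would hide that.

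**Two sites.** The figures above treat girls as independent. With 15 per site, the design effect is 1 + 14 × ICC. For an assumed ICC of 0.01 it is 1.14 (effective n = 30/1.14 = 26.3); for 0.10 it is 2.4 (effective n = 30/2.4 = 12.5). The intervals above are thus, if anything, too narrow.

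**Recruitment.** If A families are approached and 30 girls enrol, uptake is 30/A. The benchmark is met at 30 for every A, so meeting it does not inform A. An interval applies only once a denominator is set.

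**The case against.** A reader might take the point further than the documents allow.

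- *A pass means little.* Not so for completion. A true 60% passes 4.4% of the time and a true 55% passes 1.2%.
- *The completion rule is a coin toss.* When the true rate sits on the threshold, a point-estimate rule passes about half the time at any reasonable size (51.4% at n = 30, 51.1% at n = 50). That is a property of thresholds, not a fault of this plan.
- *All the benchmarks rest on 30 girls.* AIM, IAM and FIM come from parents and staff, so three of the six do not.
- *The recruitment benchmark cannot fail.* The article calls 30 a goal and leaves open whether it is achievable. The pool is girls aged 8 to 10 enrolled at two sites, so it can fail. Nor does the article say that approach and eligibility counts will go unrecorded; recruitment is to be measured from administrative data.
- *The missing progression rule is an undisclosed gap, or meeting the benchmarks is presented as readiness for a trial.* The Discussion discloses the gap openly, and the article nowhere equates the two.

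Two further objections have weight. A recruitment period or a screening log may stand in a fuller protocol, which is not shown, so only the wording of the benchmark in the article is at issue. And adding an interval does not change the chance of passing. It changes how a pass is read.

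What remains is the written contrast within one section: intervals for the secondary outcomes, and a descriptive comparison alone for the primary ones. That is a stated method, not detail left to another document.

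**Conclusion.** The point holds in limited form. The article plans intervals for its secondary outcomes but not for its primary benchmarks, and it defines recruitment success as a count equal to the sample size with no denominator or period beside it. At a bare pass, the completion estimate of 77% carries a 95% CI of about 59% to 88%: enough to argue against poor completion, not enough to tell 70% from 80%. These figures assume 30 girls enrolled and independence between girls; clustering by site would widen the interval. The sizes given for attendance and for AIM, IAM and FIM rest on assumed SDs and respondent numbers.

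This is a worthwhile and inexpensive improvement to the analysis. It is not an arithmetic error, and it does not undermine the study. The sample size is within the range the article cites.

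**What to change.** 1. **Data analysis.** State that each of these benchmarks will be reported with a 95% CI and interpreted with it: assessment completion (Wilson), mean attendance, and the AIM, IAM and FIM means. Give the last three separately for parents and staff, each with the number of respondents. Say that the intervals ignore clustering, and show results by site.
2. **Primary outcomes.** Keep the count of 30. Add enrolled over approached and enrolled over eligible, per site, within a stated recruitment period, each with a CI.
3. **Discussion (optional).** The article concedes that the lack of progression criteria may make the decision subjective. The sponsor could therefore state, before Aim 3 enrolment, how the existing benchmarks, read with their intervals, will inform the decision to proceed. Any intermediate or stop cut-offs are the sponsor's to choose, as the documents give no basis for particular values. If such a statement is added, the limitation should be reworded to match.

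The cost is a few lines of text, some extra reporting, and a log of approaches and eligibility within the administrative data already planned. No extra participants or measures are needed. The downside is that results will look less decisive, and any statement about proceeding would bind the sponsor.
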